APPENDIX 1 (a): Recruitment Flyer

APPENDIX 1 (b): Recruitment Brochure

Screening Application

APPENDIX 2: Screening Application

The Motivation to Exercise

This study is being done to determine motivational factors involved in exercise. The purpose of this study is to research the effects of exercise on motivation levels. We expect to find out whether participants change their motivation to exercise when starting an exercise program.Participants will be enrolled in a six-week exercise program and provided memberships to Choice Health and Fitness. Exercise sessions will be about one hour per day, three days per week and prescribed by a USDA researcher. Three days of baseline assessments will take place assessing body composition, physical fitness, dietary intake, and exercise motivation before the 6-week exercise program begins. Follow-up testing sessions will also take place after the 6-week exercise program. You would visit the Grand Forks Human Nutrition Research Center or Choice Health and Fitness for an information and screening visit where you will be given information about this study and complete further screening to assure that you meet eligibility criteria for participation. If you qualify for and are interested in participating in this study, you will be scheduled for the initial three baseline testing sessions before initiation of the exercise program. This study is being conducted by [name] of the Grand Forks Human Nutrition Research Center in Grand Forks, ND.

If you are interested in joining this study please answer the following questions.

How did you hear about this study?

O UND Newsletters O UND Radio

O Tidbits O City Briefs

O Flyers O Grocery Stores

O Thrift Stores O Retail Stores

O Brochure O Senior Citizens Center

O Library O Choice Health and Fitness Center

O Other:­­­­­­­­­­­­­­­________________________

Gender: Male ____ Female ____

Are you pregnant, lactating, or planning to become pregnant in the next 6 months? ** No____ Yes_____

Are you between 18 and 49 years of age? * No_____ Yes_____

Do you have any chronic medical conditions? No____ Yes_____

If yes, please check the proper box/boxes and explain.

O Diabetes

O Major health problem

Explain:_________________________

O Cardiovascular disease

Explain:_________________________

O Pulmonary disease

Explain:_________________________

O Metabolic disease

Explain:_________________________

O Orthopedic problem that limits exercise

Explain:_________________________

O Other:________________________

Explain:_________________________

Are you taking any medications, vitamins, or supplements? No____ Yes____

If yes, please list.

Do you regularly use products containing tobacco or nicotine? ** No____ Yes_____

Are you on a diet? No____ Yes_____

If yes, please explain

Do you have any medical problems that limit your ability to safely participate in physical activity? ** No____ Yes_____

Do you exercise regularly (planned and structured aerobic activity more than two times per week)? ** No____ Yes_____

Do you have high occupational physical activity (construction trades, farm work, freight mover)?

No____ Yes_____

If yes, please explain

How much do you weigh? ____________lbs.

How tall are you? _______ft. _______in.

Name: ________________________________________

Address: _________________________________________________________

Street Apt #

_________________________________________________________

City/Town State Zip Code

Email Address: _____________________________________________________

Phone Number: _____________________________________________________

Your application is complete. It will be reviewed for study eligibility. We will contact you if an

answer in your application needs to be clarified. You will be told whether or not you qualify for

the study.

If you qualify for the study, you will be invited to meet with [name] or his designee. They will discuss with you the study requirements and answer any questions you may have. During this meeting you will complete a questionnaire which will provide information about your general health and your medication and supplement use. Your height and weight will also be measured at this time.

If you have questions, please contact [name] at [contact] or [name] at [contact] or e-mail your questions to [[contact]](mailto:[contact]) or [[contact]](mailto:[contact]). Thank you.

* If YES, the screen goes to the next question. If NO, the screen shows the message “Thank

you for your interest in joining the “Compensatory Response” study. Unfortunately, you are not

eligible for this study.

** If NO, the screen goes to the next question. If YES, the screen shows the message “Thank

you for your interest in joining the “Compensatory Response” study. Unfortunately, you are not eligible for this study.

[figure not shown]

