**C. Methods**

**i. Participants and screening**: As shown in Table 1, 45 men and 45 women age 18-49 y, that range in adiposity from lean to obese (19-35 kg/m^2^) and have no contraindications for PA participation will be recruited. Subjects will be sedentary, i.e. not be regularly engaging in exercise more than once per week. They will be instructed to not enroll in an exercise program and to limit planned PA to that prescribed by the investigators for the duration of the incentive sensitization treatment. Subjects cannot have high occupational activity such as construction trades, farm workers, and freight movers who complete most of their work by hand. Additional exclusionary criteria include a liking of <3 out of 10 for all available PA modes and exercising for more than 30 min/day > 2d/wk and repeated non-compliance with completing the exercise sessions. Participants will be screened for entry criteria and will report the times/wk they engage in various types of PA.

**ii. Design:** Physical activity will be performed on stationary cardio-type exercise machines (choice each day of treadmill, elliptical, stair stepper, cycle). Each treatment will be 6 wk in duration with 3 treatment sessions/wk. Outcome testing will occur at baseline, 3, 6, 10, and 14 wks. As shown in **Table**

**1**, participants will be randomized to exposures of 0, 150, or 300 kcal/session. The 150 kcal and 300 kcal dose groups will participate in 3 physical activity sessions (days)/wk. All participants will be provided Choice Health and Fitness (CHF) memberships, the 0 kcal dose group will receive their CHF membership and exercise program after they complete the study.

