**iii. Procedures**:

Visit One: Screening and Consent

Participants will be recruited by Grand Forks Human Nutrition Research Center (GFHNRC) staff using Survey Monkey. We will leverage our partnership with Choice Health and Fitness to utilize their electronic entry records and send recruitment materials to those fitness club members who attend Choice Fitness 2 or fewer visits per week and otherwise seem to meet our other entry criteria. Various other media will be used to advertise the study. This may include brochures, print media such as the Grand Forks Herald, Dakota Student, Exponent, and Tidbits, television and radio such as the UND television and radio stations. Internet advertisements including University Research Newsletter, University Letter, HEALTHY-UND Listserv, and Work Well Newsletter may be utilized. Recruitment efforts may also include posting flyers around the Greater Grand Forks area and surrounding communities, promoting the study at expos and trade shows, and providing information on the GFHNRC website. Recruitment will continue until the study needs are met. A sample advertisement is attached (APPENDIX 1 a/b). Subjects may apply to join the study by completing the on-line application on Survey Monkey (APPENDIX 2). Eligible applicants will be invited to an information/screening appointment at the GFHNRC or CHF. During this initial visit, subjects will be informed about the study and have any questions answered. If deemed eligible and the subject desire to participate, they will be asked to provide written informed consent (APPENDIX 3). After signing the consent, subjects will fill out a demographic form (APPENDIX 4), a medical history form (APPENDIX 5), and be measured for anthropometrics. Subjects will also be provided a SenseWear device to wear for the following week to monitor free-living energy expenditure and physical activity. Questionnaires including The Preference for and Tolerance of the Intensity of Exercise Questionnaire (PRETIE-Q) (Appendix 6) [[30](#_ENREF_30), [31](#_ENREF_31)], the Discomfort Intolerance Scale [[32](#_ENREF_32)] (Appendix 7), Social norms [[33](#_ENREF_33)], Social Support and Exercise Survey (APPENDIX 8) [[34](#_ENREF_34)], the Exercise Self-Efficacy Scale (EXSE, Appendix 9) [[35](#_ENREF_35)] and the Exercise Confidence Survey (APPENDIX 10), Psychological needs satisfaction (PNSE) (APPENDIX 11), and the Behavioral Regulation in Exercise questionnaire (BREQ-3) (APPENDIX 12) will be completed by the subject at this time. The first of four dietary recalls will be completed and the subject will be scheduled for their three baseline visits at (CHF).

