
Baseline Assessment Day 1 (CHF)

Subjects will arrive at CHF at least 2 hrs after eating to complete the physical activity reinforcement task (RRV_PA_). Participants will first rate their liking of the PA and sedentary alternatives (Appendix 13). The highest rated PA and sedentary alternatives will be provided as alternatives for the RRV testing session. Additionally, treatment expectations of the study will be assessed with the Stanford Expectations of Treatment Scale (SETS) [[36](#_ENREF_36)] tailored for the current study (APPENDIX 14). The SETS tool assesses expectancy effects to be co-varied for in the statistical analyses. Participants will complete a dietary recall.

Baseline Assessment Day 2 (CHF)

Subjects will arrive at CHF at least 2 hrs after eating to complete body composition and aerobic fitness tests. Body composition will be determined by DXA and submaximal fitness tests will be completed on a motorized treadmill. Participants will complete a dietary recall.

Baseline Assessment Day 3 (CHF)

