6-Week Intervention The treatment is based on meeting the prescribed kcal expenditure as measured using the SenseWear device (described below) three times per week. The intensity, duration, and interval/ constant load nature of physical activity will not be prescribed. For approximately the first six sessions, a research assistant will be present to provide instruction on the use of the stationary exercise machines and will monitor each session for attaining the energy expenditure goal of either 150 kcal or 300 kcal. The study-related exercise will be a circumscribed and intentional bout recorded by the participant in a log book. Compliance regarding the energy expenditure of each physical activity session will be monitored by the subject and staff using an activity monitor. A research assistant will meet with the subject each week at the fitness center to download and review the activity monitor wear log (APPENDIX 20) and activity monitor data with the volunteer. Volunteers will be given feedback if the exercise bout cannot be readily identified from the activity monitor or if the bout did not meet the energy expenditure criteria. To promote external validity and minimize seasonal/weather effects, treatment sessions will occur at the fitness center. Subjects in the 0 kcal group will wear the physical activity monitor only during assessment periods. No instruction will be provided regarding dietary intake as spontaneous change in dietary intake is an outcome measure.

Week-6 Assessments (Post)

At the conclusion of the intervention, participants will follow the testing schedule outlined for the baseline assessments. Additionally, the Perceived Autonomy support questionnaire will be administered (APPENDIX 21) and subjects will be issued an activity monitor to wear for the following week and will return to CHF to return the device.

Week 10 Assessments

After four weeks of no-contact with the study investigators, subjects will follow the testing schedule outlined for the baseline assessments except they will not complete a body composition test. Subjects will be issued an activity monitor to wear for the following week and will return to CHF to return the device.

**iv. Measures**: Gender, baseline age, and baseline values of outcomes will be tested as moderators of change in RRV of physical activity (**Table 2**).

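### The screening application describes an immediate exercise program for every participant and does not mention that one third are randomly assigned to a delayed-start 0 kcal group

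*Protocol*

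**What the plan says.** Appendix 2 of the Protocol is the on-line application. Its introduction tells applicants: "Participants will be enrolled in a six-week exercise program and provided memberships to Choice Health and Fitness". It continues: "Exercise sessions will be about one hour per day, three days per week and prescribed by a USDA researcher". It places baseline tests before the six-week program and follow-up tests after it. Neither the introduction nor the questions mention chance assignment or a group that does not exercise during the study.

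The body of the Protocol describes a different experience:

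- C. Methods, ii. Design: "participants will be randomized to exposures of 0, 150, or 300 kcal/session". On the control arm: "the 0 kcal dose group will receive their CHF membership and exercise program after they complete the study".
- Table 1: 15 men and 15 women at each of the three doses.
- C. Methods, iii. Procedures, 6-Week Intervention: the treatment is an energy-expenditure target met three times a week, and "The intensity, duration, and interval/ constant load nature of physical activity will not be prescribed".

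On informing participants before entry, the Procedures section says of the screening visit: "During this initial visit, subjects will be informed about the study and have any questions answered". Written consent follows at that visit, before any baseline testing at the fitness center. On expectations it says: "The SETS tool assesses expectancy effects to be co-varied for in the statistical analyses".

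**The concern.** People decide whether to apply on the strength of this form. It describes a program and a membership that everyone receives at once. One in three of those randomised will receive neither until the study is over. Meanwhile C. Methods, i. asks all subjects not to join an exercise program during treatment and to keep planned activity to what is assigned, which for the 0 kcal group is none.

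This matters more here than in many trials. Participants cannot be blinded to exercising or not exercising. The primary outcome, RRV_PA, is how hard someone will work for access to exercise. Disappointment or a sense of restriction in one arm could plausibly move that measure, in either direction, or lead people to leave. The 0 kcal arm is one of the two comparators in Hypotheses 1 and 2, and Section D sets the recruitment goal equal to the calculated sample size, with no stated allowance for loss.

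**Working it through.** **1. The passages side by side**

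| Topic | Appendix 2 | Body of the Protocol |
| --- | --- | --- |
| Who exercises in the six weeks | Participants, without distinction | The 150 and 300 kcal groups only |
| How this is decided | Not mentioned | Randomisation to three doses |
| When membership and program are given | Implied at once | For 0 kcal, after study completion |
| Session length | About one hour | Not prescribed; set by an energy target |

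**2. Share of participants affected**

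From Table 1: (15 + 15) / 90 = 30/90 = 1/3. The staffing estimate in Section H agrees: it counts 60 participants in exercise groups, and 90 − 60 = 30.

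The wait lasts at least until the 10-week assessments in Tables 1 and 2. The Design section also lists a 14-week test, so the length of wait to be told to applicants depends on which schedule stands.

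**3. Session length**

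At any one rate of expenditure, 300 kcal takes 300/150 = 2 times as long as 150 kcal, so a single typical length cannot fit both doses at the same rate. One hour would correspond to 150/60 = 2.5 kcal/min in one group and 300/60 = 5 kcal/min in the other. The Protocol gives no expected rate, so this shows only that the statements need reconciling.

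**4. What loss in the 0 kcal arm could cost in power**

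The plan's own figure comes first. Inputs from Section D are difference 7, SD 8, α = 0.05 (taken as two-sided) and 90% power.

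n per compared arm = 2(1.960 + 1.282)² × 8² / 7² ≈ 27.5, so 28.

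This is consistent with 30 per dose (15 men plus 15 women), provided the stated 15 per group is read as a sex-by-dose cell. With 15 per compared arm, power would be only 66.9%. The rest of this check uses 30 per dose.

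Section D states the difference of 7 for the two exercise doses. Applying it to 300 versus 0 kcal is an assumption. So is the range of loss, since the Protocol gives no rate; all loss is placed in the 0 kcal arm.

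Power = Φ( 7 / [8 √(1/n₀ + 1/30)] − 1.960 )

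| Assumed loss at 0 kcal | n₀ | Power, 300 vs 0 kcal |
| --- | --- | --- |
| 0% | 30 | 92.3% |
| 10% | 27 | 91.0% |
| 20% | 24 | 89.2% |
| 30% | 21 | 86.8% |
| 40% | 18 | 83.5% |

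The only contrast that Section D powers, 150 versus 300 kcal, is unaffected by loss at 0 kcal. The loss of power is modest. Bias from selective withdrawal or disappointment cannot be computed from the Protocol.

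**5. Whether existing safeguards cover the risk**

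The expectation scale is given at baseline only. It can adjust for prior expectations but not for a reaction to allocation. Its timing relative to randomisation is not stated, although its form asks which treatment the person is going to receive. The primary model in Section D does not list it among the covariates.

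**The case against.** The strongest reply is that this is only a pre-screening form. Appendix 2 itself announces an information visit, and the Procedures section puts information, questions and written consent before baseline testing. That stands. A reader might infer that participants reach randomisation still expecting immediate exercise. The documents do not support this, because the consent form is not available and may describe the three groups in full.

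Other stronger readings are tempting and also fail:

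- **That the 0 kcal group is denied the program.** It is promised both membership and program later. The form errs on timing and on the missing randomisation.
- **That self-selection biases the comparison.** Applicants keen to exercise are selected before randomisation, so all arms are affected alike. This bears on generalising to sedentary people at large. The design needs volunteers open to exercise and screens out those who dislike every available mode.
- **That dropout will concentrate at 0 kcal by some stated amount.** No rate is given. Delayed access and the $300 of $500 tied to the end of follow-up (Section G) both work against it.
- **That the form reveals the hoped-for result.** Its sentence on motivation asks whether it changes and gives no direction, so it can stay.
- **That the one-hour figure is wrong.** It may be a rough statement of burden, and the mention of prescription fits the prescribed energy target. Only the stated length sits uneasily with the Procedures section.

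It is also fair to say that some reaction to an unblinded delayed-access control will remain however the form is worded. Clear wording removes only the avoidable part.

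**Conclusion.** The mismatch is established from the Protocol's own text. The application describes immediate exercise for participants and omits randomisation, while one third (30 of 90) start only after the study; the stated session length is not reconciled with sessions defined by energy expenditure. The consequence is less certain: a risk of avoidable disappointment or withdrawal in the 0 kcal arm, of unknown size, which the information and consent visit may already reduce. On the assumptions above, even 40% loss confined to that arm leaves 83.5% power for 300 versus 0 kcal, so the case rests on possible bias in a motivation outcome and on accurate participant-facing text. This is a minor to moderate point that is nearly free to correct.

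**What to change.** Make the introduction of Appendix 2 agree with C. Methods, ii. Design and the 6-Week Intervention text. It should state that:

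- assignment is by chance to one of three groups;
- one group begins its program and membership only after the study, with the length of the wait taken from the reconciled assessment schedule;
- session length varies with the assigned energy target, as the Procedures section now has it, or else that the two passages have been reconciled in some other way.

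Add a screening question asking whether the applicant would accept any of the three groups. It must carry the single-asterisk rule, under which NO ends the application. The double-asterisk rule makes YES disqualifying and would turn away exactly the willing applicants. The footnoted rejection messages name a different study and can be corrected in the same revision. Check the flyer, brochure and consent form for the same omission.

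The cost is a text revision with ethics-board approval. Some applicants will decline earlier, but before baseline testing has been spent on them.

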**#3. Gender: Male Female**

**#4. Race (Select Only One): American Indian or Alaskan Native**

**Asian**

**Black or African American**

**Native Hawaiian or Other Pacific Islander**

**White**

**Multi-racial**

**Unknown**

**I prefer not to answer**

**#5. Ethnicity (Select Only One): Hispanic or Latino**

**Not Hispanic or Latino**

**Unknown**

**I prefer not to answer**

**#6. Mailing Address:**

**#7. *Preferred* method of Contact: _ E-mail Cell Phone Text**

**#8. E-mail Address:**

**#9. Cell Phone Number:**

**#10. Cell Phone Carrier:**

APPENDIX 5: Health History

# Health History Questionnaire

NAME: ___________________________ DATE: __________________________

Birthdate: ______________________________Gender: Male Female

Height:_____________________ Weight:________________ BMI_______

Person to contact in case of Emergency:

Name: _______________________________ Phone: ______________________

1. Are you taking any medications or drugs?

If YES, please list medication, dose and reason: Medication:_________________Dose:_____________Reason:_______________ Medication:_________________Dose:_____________Reason:_______________

Medication:_________________Dose:_____________Reason:_______________

Medication:_________________Dose:_____________Reason:_______________

*Use the back for more space*

YES NO

□ □ 1. Has your doctor ever said that you have a heart condition and that you should only do

physical activity recommended by a doctor?

□ □ 2. Do you feel pain in your chest when you do physical activity?

□ □ 3. In the past month, have you had chest pain when you were not doing physical activity?

□ □ 4. Do you lose your balance because of dizziness or do you ever lose consciousness?

□ □ 5. Do you have a bone or joint problem that could be made worse by a change in your

physical activity?

□ □ 6. Is your doctor currently prescribing drugs (for example, water pills) for your blood

pressure or heart condition?

□ □ 7. Do you know of any other reason why you should not do physical activity?

| **General Health Questions:** | **Yes** |  | **No** |
| --- | --- | --- | --- |
| **History of heart problems, chest pain or stroke** |  |  |  |
| **Increased blood pressure** |  |  |  |
| **History of breathing or lung problems** |  |  |  |
| **Diabetes or thyroid disease** |  |  |  |
| **Seizures, tremors or severe headaches** |  |  |  |
| **Arthritis or other bone problems** |  |  |  |
| **Increased blood cholesterol** |  |  |  |
| **Use products containing tobacco or nicotine regularly** |  |  |  |
| **Recent surgery (last 12 months)** |  |  |  |
| **Any other chronic illness or condition Please List:** |  |  |  |

